## Abstract

**Background:** Major depressive disorder (MDD) is a serious public health problem with high lifetime prevalence (4.4–20%) in the general population. The monoamine hypothesis is the most widespread etiological theory of MDD. Also, recent scientific data has emphasized the importance of immuno-inflammatory pathways in the pathophysiology of MDD. The lack of data on the magnitude of brain neuroinflammation in MDD is the main limitation of this inflammatory hypothesis. Our team has previously demonstrated the relevance of [18F] DPA-714 as a neuroinflammation biomarker in humans. We formulated the following hypotheses for the current study: (i) Neuroinflammation in MDD can be measured by [18F] DPA-714; (ii) its levels are associated with clinical severity; (iii) it is accompanied by anatomical and functional alterations within the frontal-subcortical circuits; (iv) it is a marker of treatment resistance.

**Methods:** Depressed patients will be recruited throughout 4 centers (Bordeaux, Montpellier, Tours, and Toulouse) of the French network from 13 expert centers for resistant depression. The patient population will be divided into 3 groups: (i) experimental group—patients with current MDD (*n* = 20), (ii) remitted depressed group—patients in remission but still being treated (*n* = 20); and, (iii) control group without any history of MDD (*n* = 20). The primary objective will be to compare PET data (i.e., distribution pattern of neuroinflammation) between the currently depressed group and the control group. Secondary objectives will be to: (i) compare neuroinflammation across groups (currently depressed group vs. remitted depressed group vs. control group); (ii) correlate neuroinflammation with clinical severity across groups; (iii) correlate neuroinflammation with MRI parameters for structural and functional integrity across groups; (iv) correlate neuroinflammation and peripheral markers of inflammation across groups.

**Discussion:** This study will assess the effects of antidepressants on neuroinflammation as well as its role in the treatment response. It will contribute to clarify the putative relationships between neuroinflammation quantified by brain neuroimaging techniques and peripheral markers of inflammation. Lastly, it is expected to open innovative and promising therapeutic perspectives based on anti-inflammatory strategies for the management of treatment-resistant forms of MDD commonly seen in clinical practice.

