The primary objective of this study is to compare the TSPO distribution volume assessed in PET (DPA-714) between patients with moderate-to-severe MDD (“currently depressed group”) treated with antidepressants considered as ineffective (and before a new treatment strategy is initiated as recommended) and normal healthy subjects without any antidepressant treatment (“control group”).

The secondary objectives are to: (i) compare the TSPO distribution volume assessed by PET among the currently depressed patients, those in clinical remission but still being treated with antidepressants (“remitted depressed group”) and normal controls; (ii) correlate the severity of depressive symptoms, suicidal risk, and central neuroinflammation intensity evaluated by PET in the currently depressed group; (iii) measure the correlation between the distribution volume of PET-assessed TSPO and a series of structural (microstructural integrity, cortical thickness, intracerebral iron content) and functional (connectivity force of the default-mode network) MRI markers in the three subject groups; (iv) measure the correlation between the distribution volume of PET-assessed TSPO and the plasma concentrations of peripheral inflammatory markers in the three subject groups.

We formulated the following hypotheses: (i) Neuroinflammation in MDD can be measured by [18F] DPA-714; (ii) its levels are associated with clinical severity; (iii) it is accompanied by anatomical and functional alterations within the frontal-subcortical circuits that are highly involved in MDD; (iv) it is a marker of treatment resistance. If these hypotheses are confirmed, then this study will enhance our understanding of the role of these neuroinflammatory processes in MDD. This breakthrough could have a significant long-term therapeutic impact by developing more specific antidepressant drugs with potent anti-inflammatory action and/or medicines primarily targeting neuroinflammation.

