### Eligibility criteria

The following inclusion criteria will be applied to all study groups: (1) men and women aged 25 to 55 years, (2) affiliated to a Social Security scheme, (3) able to understand the given instructions and information about the study design, and (4) have provided written informed consent. The currently depressed group will include patients: (1) meeting the DSM-5 criteria of MDD diagnosis, (2) experiencing significant depressive symptoms (as indicated by a score > 20 on the Montgomery and Asberg Depression Rating Scale, MADRS), (3) receiving an ineffective antidepressant treatment (a well-conducted treatment at an appropriate dosage for a minimum of 6 weeks), and (4) showing plasma antidepressant levels within the therapeutic range after at least 1 additional week of antidepressant treatment with unchanged dosage. The remitted depressed group will comprise patients: (1) meeting the DSM-5 criteria of MDD diagnosis, (2) achieving remission for at least 8 consecutive weeks according to the standard DSM-5 criteria (as indicated by a MADRS score <10), and (3) receiving antidepressant medications at a stable dosage for 1 week or more. The control group will include normal healthy subjects free from any current or past psychiatric conditions and without peripheral signs of inflammation (as indicated by circulating concentrations of hs-CRP <5 mg/L).

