#### Analysis of PET imaging data

To evaluate the brain kinetics of [18F] DPA-714, PET images will be co-recorded on the MNI atlas with PMOD® software. To construct time-activity curves of [18F] DPA-714, the PET images will be segmented into 13 regions of interest (ROI): precuneus, anterior cingulum, posterior, frontal, temporal, parietal, occipital cingulum, hippocampus, semi-oval centrum, anterior putamen, posterior putamen, caudate nucleus, and intersections, as defined in the MNI-AAL atlas. The binding potential (BP) is the ratio of B_max_ (receptor density) to KD (dissociation constant): BP = B_max_ / KD shall be calculated. Additionally, the distribution volume ratio (DVR) will be estimated from the region of interest and a reference region using, for example, Logan graphical analysis (66) with the cerebellum as reference region for the images obtained between 0 and 90 min (46). In this study, the DVR will be calculated as the slope of the linear part of the Logan analysis using PMOD software. We will calculate the BP for the 13 ROIs mentioned above, as well as for the entire brain.

For the primary hypothesis, PET data will be analyzed by multivariate ANOVA with TSPO Volume in the 13 ROIs as the dependent variables and diagnosis and genotype as fixed factors. Main effects will be considered significant at the conventional *P* ≤ 0.05. Effects in each region, will be analyzed by univariate ANOVA.

As a secondary analysis, a MANOVA including every brain region sampled (including all cortical and subcortical regions) will be performed to assess the effect of diagnosis on TSPO Volume. A partial correlation will be used in a secondary analysis to quantitate the relationship between TSPO Volume in the primary regions of interest and severity of symptoms of MDD measured by total MADRS score.

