#### Analysis of all data

PET and MRI imaging, clinical symptomatology and biological markers. PET and MRI images will be co-recorded using a method previously used by our team (71) [e.g., 71] so that the maps of all multimodal markers have the spatial consistency needed for their statistical comparison. Firstly, for each marker map, we will perform *t*-tests to compare the groups with each other (SPSS 25.0). This will allow us to quantify the structural, functional and inflammatory alterations that characterize each group (i.e., treatment-resistant MDD vs. control, responsive MDD vs. control, treatment-resistant MDD vs. responsive MDD). Secondly, we will verify that there is no spatial collocation between the atrophy marker (MRI) and the inflammation marker (DPA714 -PET) that can induce a different interpretation of PET results. Finally, we will correlate the inflammation marker maps with the structural and functional marker maps generated with MRI. This will allow us to understand whether neuroinflammation is linked to brain changes (e.g., iron deposits, functional alteration).

To study the correlation between the severity of depressive symptoms, suicide risk and the intensity of neuroinflammation, graphic representations will be made to observe the distribution of these data in the two groups concerned. The Pearson correlation coefficient will be calculated in each instance. The same analysis strategy will be used to measure the correlation between plasma concentrations of biological markers of peripheral inflammation and the intensity of neuroinflammation in the three study groups.

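### The correlation of TSPO with depression severity has no single population or method; if depressed and remitted patients are pooled, a group difference would appear as a severity association

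*Protocol article*

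**What the plan says.** **Population.** Three places describe the correlation of neuroinflammation with severity.

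- Abstract: "correlate neuroinflammation with clinical severity across groups".
- Introduction, secondary objective (ii): "correlate the severity of depressive symptoms, suicidal risk, and central neuroinflammation intensity evaluated by PET in the currently depressed group".
- Analysis of all data: "graphic representations will be made to observe the distribution of these data in the two groups concerned". The groups are not named. Depressed and remitted patients are the natural inference.

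**Method.** Two are given.

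- Analysis of PET imaging data: "A partial correlation will be used in a secondary analysis to quantitate the relationship between TSPO Volume in the primary regions of interest" and total MADRS. Neither the population nor the controlling variables are named.
- Analysis of all data: "The Pearson correlation coefficient will be calculated in each instance". No covariate or group term is mentioned. The same strategy is then extended to peripheral inflammatory markers in the three study groups.

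**Related statements.**

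- PET assessment says that TSPO genotype affects tracer affinity and will enter the data analysis as a covariate.
- Eligibility criteria sets the depressed group's MADRS limit ("as indicated by a score > 20 on the Montgomery and Asberg Depression Rating Scale, MADRS") and the remitted group's ("as indicated by a MADRS score <10").
- Subjects states the expectation that neuroinflammation is lower in remitted patients under effective treatment. It gives no size for this difference.

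**The concern.** These statements cannot all describe one analysis. The population is 20, 40 or 60 subjects, depending on which statement is followed and whether groups are combined. The coefficient is either adjusted or not.

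The choice is not neutral. Eligibility leaves no patient with a MADRS score from 10 to 20, so across both patient groups MADRS mostly tells which group a patient belongs to. A coefficient pooled over the two groups would then largely repeat the depressed-versus-remitted comparison, which is already a secondary outcome. It could be read as separate evidence for hypothesis (ii), that neuroinflammation is associated with severity, even if severity and TSPO were unrelated within each group. The Conclusion section gives the severity link high prominence. Leaving population and method open also allows the choice to be made after the data are seen.

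A plain Pearson coefficient also leaves the genotype-driven part of the PET signal in the data, although the article says that this will be adjusted for.

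**Working it through.** **1. The plan's own figure.** The article gives no power or detectable size for this correlation. Its only figure is 80% power with 20 per group for depressed versus control, based on 12.3 versus 9.3 ml/cm³ (difference 3.0), with no SD. Solving for the SD gives about 3.39 by the normal approximation (d = 3.0/3.39 = 0.886) or 3.30 by the t-test (d = 3.0/3.30 = 0.909). The 80% can therefore be neither confirmed nor refuted. It is used here only to set the upper end of a range for d. It belongs to the depressed-versus-control contrast. The depressed-versus-remitted difference is not given.

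**2. How close MADRS is to a group label.** Assume depressed 28 (SD 5) and remitted 5 (SD 3), 20 each.

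- Between-group variance: (23/2)² = 132.25.
- Mean within-group variance: (25 + 9)/2 = 17.
- Total: 149.25.
- Correlation of MADRS with group: √(132.25/149.25) = 0.94.

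**3. Pooled r when the within-group correlation is zero.** With TSPO in SD units and a group difference d:

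r = (ΔMADRS × d / 4) / √[total MADRS variance × (1 + d²/4)]

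- d = 0.5: (23 × 0.5/4) / √(149.25 × 1.0625) = 2.875/12.59 = 0.23.
- d = 0.91: (23 × 0.91/4) / √(149.25 × 1.207) = 5.23/13.42 = 0.39.

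The two-sided 5% critical value of r is 0.312 at n = 40.

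**4. How often p < 0.05.** Simulation of 20,000 trials per scenario, 20 + 20 patients, zero within-group correlation. Each cell gives pooled r from the formula and the share of trials significant.

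| Assumed MADRS, depressed vs remitted | d = 0 | d = 0.3 | d = 0.5 | d = 0.7 | d = 0.91 |
|---|---|---|---|---|---|
| 24 (4) vs 7 (3) | 0; 4.7% | 0.14; 13.5% | 0.22; 29.7% | 0.31; 50.4% | 0.38; 72.0% |
| 28 (5) vs 5 (3) | 0; 5.1% | 0.14; 13.7% | 0.23; 30.2% | 0.31; 52.4% | 0.39; 74.3% |
| 32 (6) vs 4 (3) | 0; 4.7% | 0.14; 14.0% | 0.23; 30.5% | 0.31; 53.0% | 0.39; 75.3% |

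At d = 0.886 the shares are 71-73%. A separate run of 40,000 trials with 30 (5) vs 5 (2.5) gave 31% at d = 0.5 and 76% at d = 0.909. MADRS was drawn from normal distributions not cut at the eligibility limits; cutting them would separate the groups further.

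**5. Alternatives in the same simulated trials.** The correlation within the depressed group alone, and the pooled correlation adjusted for group, were each significant in about 5% of trials at every d.

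**6. All three groups pooled.** With controls at MADRS 2 (2) and at the remitted TSPO level (n = 60), the share is about 40% at d = 0.5 and 86% at d = 0.886.

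**7. What 20 patients can detect.** By Fisher's z, the smallest r with 80% power is tanh[(1.96 + 0.8416)/√(n − 3 − k)], where k is the number of covariate terms.

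- k = 0: tanh(2.8016/√17) = 0.59.
- k = 1: tanh(2.8016/√16) = 0.60.
- k = 2: tanh(2.8016/√15) = 0.62.

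**The case against.** **Pooling is not stated.** A reader might infer that the plan commits to a Pearson coefficient pooled over groups. It does not. The Abstract names no method, and the Pearson sentence names no pooled sample. Its closing words can equally mean one coefficient per group, which has no two-cluster problem. This objection stands, so the inflation is conditional on pooling.

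**The Abstract is shorthand.** It uses the same phrase for all four secondary objectives, so it is weak evidence of a third population. That is fair. The substantive conflict is between objective (ii) and Analysis of all data.

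**The percentages are not a type I error rate for the pooled coefficient.** When the groups differ in TSPO, the pooled correlation truly is non-zero. The result misleads only if it is read as an association among patients within a group, which hypothesis (ii) does not spell out. This also stands. The figures show how often a pure group difference would be reported as a severity correlation.

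**The sizes are assumed.** The MADRS means and SDs and the depressed-versus-remitted d are not in the article. This is true, although the results barely change over the MADRS range tried.

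**Covariates may be in the full plan.** An article may leave the list of partialled-out variables to the full plan, and PET assessment makes a general commitment on genotype. That answers the silence in the partial-correlation sentence. It does not reconcile that sentence with an unadjusted Pearson coefficient.

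**Other inferences not supported.** A reader might add that Pearson is unsuitable for the cytokines or for single C-SSRS items. The article gives no cytokine distributions and does not say that single items enter a correlation. Nor does any section imply adjustment for age and sex here.

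**Conclusion.** The point holds as an inconsistency in the current text. The severity correlation has one population in objective (ii), a different and unnamed one in Analysis of all data, and a loose one in the Abstract. It also has two methods, one of which leaves out the promised genotype covariate. These are positive statements that disagree, so condensation into an article does not explain them.

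The consequence is conditional. If depressed and remitted patients are pooled without a group term and their TSPO differs, as the article expects, the difference will appear as a severity association. With no within-group correlation and the assumed MADRS values, r is about 0.23 with about 30% of trials significant at d = 0.5, and about 0.39 with about 71-76% significant at d of about 0.9. At d = 0, or with per-group coefficients, the rate stays near 5%. The same caution applies to the peripheral markers only if the three groups are combined and both variables differ by group.

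This affects a secondary analysis and leaves the primary comparison untouched. It should be corrected before the data are analysed.

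**What to change.** State one analysis and use it in the Abstract, the objectives, Analysis of PET imaging data and Analysis of all data: a partial correlation of TSPO with total MADRS in the currently depressed group, adjusted for TSPO genotype. Replace the unnamed two groups and the plain Pearson sentence accordingly.

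For any correlation that involves more than one group, whether severity or peripheral markers, either calculate it within each group or include group as a covariate alongside genotype.

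The cost is a wording change, with no new data or visits. The drawback is limited sensitivity: with 20 patients, 80% power needs a true r of about 0.6, slightly more with each added covariate. A null result would therefore be weak evidence against an association, and the plan should say so.

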### Ethics

This protocol has been approved by an independent national research ethics committee (CPP Île-de-France 6; RC31/16/8918 CPP/41-17). The protocol was also registered in the clinical trial database (NCT03314155).

## Discussion

MDD is a highly prevalent disorder associated with a considerable loss of quality of life, increased mortality rates, and substantial economic costs. Because of a lack of knowledge about this disease, many patients remain untreated. Among patients given adequate medication, only 35% will achieve clinical remission. Furthermore, the probability of recurrences increases with the number of previous depressive episodes (7, 72, 73). Greater knowledge about the pathophysiology of MDD seems therefore necessary.

The inflammatory approach is an extension of the early monoamine theory of MDD, which has remained the only explanatory model for many years (74). Indeed, in inflammatory conditions, cytokines regulate monoamine neurotransmitters, notably serotonin. The most relevant mechanism involves activation of the inducible enzyme indoleamine 2,3 dioxygenase (IDO) which degrades tryptophan (TRP) into Kynurenine (KYN). Yet, TRP is a precursor of serotonin, meaning serotonin levels will be decreased (23). Similarly, inflammation is associated with lowered dopamine function (75). In addition, the pro-inflammatory cytokines appear to stimulate the hypothalamic-pituitary-adrenal axis, as one of the major stress-responsive biological system (76, 77). There is a cascade reaction at the hypothalamic and pituitary levels with an elevation in CRH and ACTH concentrations. At the adrenal level, there is an increase in cortisol synthesis. However, high plasma cortisol levels fail to decrease efficiently the activation of the transcription factor NF-kB levels controlling the expression of pro-inflammatory genes in the CNS (23). These data seem to fit into a larger framework for the pathophysiological knowledge of MDD. Indeed, the immune-mediated mechanisms occupy a pivotal position among the neurobiological determinants of MDD. Inflammation has extensively been found to generate serious deficits in synaptic plasticity as well as profound disturbances of neurotransmitter systems, underlying the cognitive and behavioral symptoms of MDD. Indeed, preclinical models of stress-induced depression have shown how peripheral and central immune components can initiate and propagate inflammatory signals in the brain. Microglia is the primary mediator of these neuroinflammatory responses and, when exposed to stress, exhibit profound morphological and functional alterations that play a key role in the development of anxious and depressive behaviors. In addition, neuroplasticity and behavioral deficits occur when microglia is distanced from homeostatic processes and engaged toward maladaptation in response to stress (78). Nevertheless, it is important to emphasize the fact that those abnormal inflammatory processes seem to take place only a subset of depressed patients (78, 79), as attested by high peripheral levels of the inflammatory marker CRP above 3 mg/L found only in 16% of a large sample of depressed patients (79), leading to consider MDD not as the sole result of an impaired immune function. Despite these considerations, the findings supporting the inflammatory hypothesis of MDD could open up significant opportunities for medical management of those depressed patients with inflammatory profile.

Altogether, these findings should open up new opportunities for MDD medical management. Two meta-analyses (80, 81) have highlighted the anti-inflammatory role of serotonin reuptake inhibitors (SSRIs). The meta-analysis by Hannestad et al. (81) has found decreased IL6 and IL-1β serum concentrations in successfully treated patients with MDD, although these data remain contradictory. In contrast, several studies have documented that depressed patients having high baseline peripheral inflammatory cytokines (IL-6, TNF-alpha) and gene expression fails to respond adequately to SSRIs (82–84). Therefore, the use of anti-inflammatory molecules such as anti-TNFα is a new research avenue for treating MDD. Reason and colleagues have shown infliximab to be effective for treating MDD in depressed patients with a CRP greater than 5 mg/L (85). In their meta-analysis, Fond et al. (80) and Abbasi et al. (86) suggested combining a COX2 inhibitor to block the production of pro-inflammatory prostaglandins with an antidepressant for the treatment of MDD. Relationships were found between an improvement in depressive symptoms and decreasing circulating levels of IL-6. In addition, brain stimulation techniques such as electroconvulsive therapy currently proposed for the management of resistant forms of MDD appear to modulate the immunoinflammatory cascade (87).

In this context, the development of biomarkers to differentiate MDD from treatment-resistant MDD is a major challenge. Demonstrating different clinical clusters in MDD through neuroinflammation could lead to more personalized patient care. Some symptoms of depression such as anhedonia, loss of interest, and psychomotor retardation are associated with biomarkers of peripheral inflammation (88–90). However, this data mainly refers to peripheral markers of inflammation. Will we find this association with neuroinflammation in our study? In a previous study, Setiawan et al. showed that the highest TSPO distribution volume occurred in MDD patients with the most severe depressive symptoms. But they did not demonstrate any relationship between neuroinflammation and peripheral markers of inflammation. Importantly, there is no available data on the TSPO distribution volume in depressed patients in clinical remission (45). Moreover, to our knowledge, although relationships with active suicidal ideation was recently established (91), there is no scientific study supporting a link between certain symptoms of MDD such as anhedonia, loss of interest and psychomotor retardation with neuroinflammation, despite available data on peripheral inflammation markers.

We will therefore try to highlight at the level of the CNS what existing scientific data currently finds at the peripheral level to attempt to show a significant correlation between peripheral and central modifications in MDD.

